#### 2.3.3. Measurements and Data Collection Plan

For patients receiving care in the PCC for head injuries which are acute, the primary patient outcome measure will be time to symptom resolution. The symptoms include vertigo, convergence insufficiency, cognitive functioning, psychological functioning, sleep disorders, and headache. For patients with epilepsy or neuroimmunological disorders which are chronic, the primary outcome measures include both disease activity and patient adherence to medication. Disease activity for epilepsy is measured by seizure frequency, and that for neuroimmunological disorders is measured by clinical (relapses) or radiological (MRI scan abnormalities) activity after initiation of immunotherapy. Medication adherence is based on patient self-reporting and is documented during each clinic visit. Secondary outcomes are process outcomes directly related to IPC for each clinic: rate of identification of symptoms by AHP for PCC, completion rate of screening for medication adherence, time to initiation of immunotherapy for NC, and tolerance and complications for EC. In addition to outcome measures, we will also collect data on patients’ demographic and clinical characteristics at the baseline (i.e., when they were first referred to these clinics), and treatment regimen during the study period. All data will be extracted from electronic medical records upon appropriate institutional approval.

Following the TDABC methodology [22], calculation of the cost of care will involve specification of essential care activities along each care pathway, estimation of time spent on each activity by each group of HCP, and ascertainment of the unit manpower cost for each group of HCP. We will first map the care pathway consisting of all essential care activities in sequential order for each of the three selected clinics following the best practice of process mapping [28]. Training will be provided to the whole study team by one of the study team members (EL) who has experience in process mapping. The training serves to equip the study team with necessary knowledge of the importance and procedure of this step. We will also engage an expert in clinical operations from the Support Operations and Strategic Management Analytics Department in NNI to co-develop these care pathways. After the care pathways are drawn up, we will survey the HCP performing each activity on each pathway to estimate the average amount of time required to carry out the specific activity using a pre-designed form. If more than one individual from the same HCP group is involved in a specific activity, the average of their estimates will be used as the time taken for that group of HCP for that specific activity. The unit cost data for each group of HCP will be obtained from the finance department of the institution.

#### 2.3.4. Analysis Plan

Survival analysis will be used to characterize the primary outcome of time to symptom resolution for patients in PCC and the process outcome of time to initiation of immunotherapy for patients in NC. Cox proportional hazards regression analysis will be performed to examine these time-to-event outcomes after adjusting for the baseline demographic, clinical characteristics, and the treatment regimen during the follow-up period. Generalized Linear Mixed Models (GLMM) will be used to analyze the longitudinal primary outcomes of patients in NC and EC from the shortest period of one year to the longest period of eight years adjusting for baseline characteristics and treatment regimen during the follow-up period. Other process outcome results will be obtained through simple arithmetic calculations.

We will calculate the cost of each activity along the care pathway by multiplying the time spent on each activity by a specific HCP and the unit cost for the HCP performing the activity. The cost of an episode of care will be the sum of the costs of all activities on the care pathway. The concept of ‘episode of care’ in this protocol will be determined by the care pathway of the respective clinics. The total cost for each clinic will be calculated by multiplying the cost of each episode of care by the volume of patients treated during the study period.

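### The Cox and mixed models adjust for treatment received during follow-up, a post-baseline variable; for time to immunotherapy this makes the model circular

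*Protocol article*

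**What the plan says.** The Protocol article, section 2.3.4 (Analysis Plan), uses one Cox specification for two outcomes. These are the PCC primary outcome, time to symptom resolution, and "the process outcome of time to initiation of immunotherapy for patients in NC". Both are to be examined "after adjusting for the baseline demographic, clinical characteristics, and the treatment regimen during the follow-up period".

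The same section analyses the longitudinal primary outcomes of NC and EC with generalized linear mixed models (GLMMs), over follow-up running "from the shortest period of one year to the longest period of eight years", again "adjusting for baseline characteristics and treatment regimen during the follow-up period".

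Section 2.3.3 (Measurements and Data Collection Plan) fixes the timing. Patient characteristics are collected "at the baseline (i.e., when they were first referred to these clinics), and treatment regimen during the study period", so the regimen is listed apart from the baseline data. The same section counts NC disease activity as "activity after initiation of immunotherapy". It introduces the group that contains time to immunotherapy with the words "Secondary outcomes are process outcomes directly related to IPC for each clinic".

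**The concern.** A covariate measured after time zero can be a consequence of the outcome process or of the care being evaluated. Here it can be both, and it enters every main model for the PCC, NC and EC primary outcomes as well as one NC process outcome.

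- **NC, time to immunotherapy.** The covariate contains the event or comes after it, so the fitted model has no useful interpretation.
- **PCC, symptom resolution.** A patient who recovers quickly has little time to receive later therapies. Having received a therapy can then act as a marker of slow recovery.
- **NC and EC mixed models.** A seizure or relapse can prompt a change of regimen, so the covariate can be affected by earlier values of the outcome.
- **Interpretation.** Section 1.3 says Study 1 assesses the impact of interprofessional care on patient outcomes. The regimen is plausibly part of what the team delivers. Results net of it do not describe the total result of team care, and they are hard to set against published outcomes, which is the comparison that section 3 (Conclusions) relies on.

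**Working it through.** The plan gives no sample size, event count or expected hazard ratio for these models, so there is no figure of its own to reproduce. The check is logical for NC and illustrative for PCC.

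**1. Is the regimen post-baseline?** Section 2.3.3 puts baseline at first referral, and section 2.3.4 takes the regimen over follow-up. It is therefore post-baseline by the plan's own definitions.

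**2. Time to immunotherapy.** Let T be the time from referral to immunotherapy and C the end of follow-up. The event indicator is d = 1 if T ≤ C. If the regimen includes immunotherapy, the covariate is x = 1 if immunotherapy was received by C, so x = d for every patient.

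- *Fixed coding.* Suppose n1 patients with x = 1 and n0 with x = 0 are at risk at an event time. That event contributes exp(b) / (n1·exp(b) + n0) to the partial likelihood. This rises with b whenever n0 > 0, so b has no finite estimate.
- *Time-dependent coding.* Just before each event, x = 0 for everyone still at risk, so the covariate carries no information. If it is switched on at the event itself, only the patient with the event has x = 1, and the estimate again diverges.
- *Simulated check* (assumed: 200 patients, median 90 days, censoring at 365 days). There were 187 events, 0 events without immunotherapy and 0 non-events with it. The remaining 200 − 187 = 13 patients had neither.

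Any regimen after initiation post-dates the event. Only treatments given before initiation, coded as time-dependent, could enter legitimately, and the text makes no such restriction.

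**3. PCC symptom resolution.** All inputs here are assumptions: 200 patients, exponential resolution time T, exponential therapy start S independent of T (so the true hazard ratio is 1.0), censoring at 365 days, 30 replicates per scenario. Fixed coding sets x = 1 if S falls before the end of the patient's own follow-up. Time-dependent coding switches x from 0 to 1 at S.

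| Median T (days) | Median S (days) | HR, fixed | HR, time-dependent |
|---|---|---|---|
| 60 | 30 | 0.17 | 1.00 |
| 60 | 60 | 0.24 | 1.00 |
| 60 | 120 | 0.36 | 1.01 |
| 90 | 30 | 0.14 | 1.04 |
| 90 | 60 | 0.22 | 1.01 |
| 90 | 120 | 0.33 | 0.96 |
| 180 | 30 | 0.08 | 1.09 |
| 180 | 60 | 0.14 | 0.94 |
| 180 | 120 | 0.28 | 1.03 |

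A hand check without censoring shows the mechanism. With rates λ for T and μ for S, mean T is 1/(λ+μ) in the never-treated and 1/(λ+μ) + 1/λ in the ever-treated. The crude rate ratio is therefore λ/(2λ+μ) = 1/(2 + median T / median S). For medians of 90 and 60 days this is 1/(2 + 1.5) = 0.29. That is not the Cox estimate (0.22 in the table), but it is likewise far below 1 for a therapy that does nothing.

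**4. Mixed models.** For EC, seizure frequency and regimen can both change throughout follow-up. For NC, disease activity is counted only once immunotherapy has begun, so the starting regimen precedes the outcome window. Only later changes can be responses to relapses or MRI findings. Immortal time is not the right description of this problem. It is conditioning on a treatment affected by prior outcome, and time-updating alone does not remove it.

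**The case against.** The strongest reply is that the plan never says the regimen is a fixed covariate. Its wording fits a time-dependent covariate equally well, and a condensed article may leave that detail to an analysis plan not shown here. This stands. A reader might infer that the plan necessarily creates immortal-time bias, but the document does not support that. The bias is conditional on fixed coding, and under time-dependent coding the illustration returns hazard ratios near 1.0.

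A reader might also infer that the adjustment removes the team's effect. That does not hold either. Section 3 says the design is single-arm, with only a non-statistical comparison against published results. Every patient receives team care, so no model has a team term to remove. The narrower point, that regimen-adjusted results omit part of the team's care, remains.

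Three further replies have weight. Section 2.3.4 first uses survival analysis to characterize the two time-to-event outcomes, and unadjusted summaries of that kind do not involve the regimen. The simulated hazard ratios concern only the regimen coefficient, which the plan never names as a quantity of interest; they do not measure bias in baseline-covariate effects or adjusted outcomes. And one short sentence covers two clinics without defining regimen for each, so the authors may have meant to leave immunotherapy out of its own model.

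That last reply does not rescue the text. Adjusting for follow-up regimen is a stated analysis choice, applied without exception to time to immunotherapy.

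**Conclusion.** The point holds in this form: the plan is wrong as written in adjusting its main models for a post-baseline regimen.

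- **Time to immunotherapy (NC, secondary process outcome).** The model is circular. This follows from the definitions, given that the regimen includes immunotherapy, and needs no numerical assumption.
- **Symptom resolution (PCC, primary).** There is a conditional risk of immortal-time bias in the regimen coefficient and in estimates adjusted for it. If coding is fixed, the distortion can be large: 0.08 to 0.36 against a true 1.0. Those figures rest wholly on assumed inputs and indicate direction and plausible scale only.
- **Disease activity (NC and EC, primary).** The covariate can be driven by earlier seizures or relapses; in NC this concerns only regimen changes after immunotherapy starts. The size cannot be derived from the document.
- **All adjusted results.** They do not describe the total result of team care and compare poorly with published outcomes.

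Unadjusted survival summaries are not affected.

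**What to change.** Amend section 2.3.4 in three places.

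1. Adjust the main Cox and mixed models for variables known at first referral only. Regimen at referral may be one of them.
2. State that the time-to-immunotherapy model contains no follow-up regimen.
3. If associations with regimen are wanted, report them in a separate model labelled exploratory, with regimen as a time-updated covariate. The label matters most for the mixed models, where time-updating does not remove the feedback from earlier outcomes.

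The cost is a change of wording and a little more programming for the time-updated coding. Regimen data are already to be extracted from the medical records, although time-updated coding also needs the dates of regimen changes. The real downside is that the main models will no longer account for regimen differences between patients. Those differences can be described alongside the results.

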#### 2.3.2. Study Sample

The population for population health in this study refers to patients with neurological disorders receiving care from the three selected team-based practices in NNI. For the assessment of patient outcomes, all patients who have been receiving care in the three selected team-based clinics since the start of these clinics (2021 for PCC, 2013 for NC, 2014 for EC) and have at least one-year follow-up period as of July 2022 will be included in the study sample.

The calculation of the cost of care does not involve sampling. We will survey all HCP involved in delivering care in the three selected clinics at the time of the study on the average amount of time they spend on each of the activities specified in a care pathway.

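### Epilepsy Clinic tolerance and complications are left to simple arithmetic with no time basis, although follow-up in that clinic runs from 1 to about 8 years

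*Protocol article*

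**What the plan says.** Section 2.3.3 of the protocol article lists the secondary (process) outcomes clinic by clinic: "rate of identification of symptoms by AHP for PCC, completion rate of screening for medication adherence", followed by "time to initiation of immunotherapy for NC, and tolerance and complications for EC".

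Section 2.3.4 then assigns methods. Survival analysis and Cox regression cover time to symptom resolution in the Persistent Concussion Clinic (PCC) and "the process outcome of time to initiation of immunotherapy for patients in NC", the Neuroimmunology Clinic. Generalized linear mixed models cover the longitudinal primary outcomes of NC and EC, over follow-up "from the shortest period of one year to the longest period of eight years". The paragraph closes with the rule for everything else: "Other process outcome results will be obtained through simple arithmetic calculations". EC tolerance and complications are named nowhere else in the analysis plan, so this rule governs them.

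Section 2.3.2 sets the sample: all patients since each clinic opened (2014 for EC) who "have at least one-year follow-up period as of July 2022".

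**The concern.** Complications accumulate with observation time, and so does intolerance if it is counted as an event. A patient seen for eight years has had far more opportunity to be recorded with one than a patient seen for one year, even if care and underlying risk are identical. The same paragraph of the plan recognises the spread of follow-up and handles time explicitly for other outcomes, but for this one it names a method with no time basis.

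The Conclusions section explains that the study is single-arm and that findings will be interpreted by a non-statistical comparison with published outcomes for the same diseases. No internal comparator shares the same follow-up mix. If EC complications and tolerance enter that comparison, a crude proportion could make the clinic look better or worse than a published series merely because its patients were watched for a shorter or longer time.

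**Working it through.** **Inputs from the article.** EC start year 2014, PCC 2021, NC 2013; cut-off July 2022; minimum follow-up 1 year (section 2.3.2). Stated longest follow-up 8 years (section 2.3.4, given for the mixed models of the NC and EC primary outcomes). The article gives no event rate, sample size or follow-up distribution, so every rate below is an assumption.

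**Step 1: the plan's own follow-up figure.** The opening months are not stated, so each clinic is bracketed between a January and a December start.
- EC: 2022 − 2014 + 6/12 = 8.5 years (January) down to 2022 − 2014 − 1 + 7/12 = 7.6 years (December). The stated 8 years fits.
- PCC: at most 2022 − 2021 + 6/12 = 1.5 years, so with the one-year minimum the span is 1 to 1.5 years.
- NC: 8.6 to 9.5 years. Its only process outcome with a named analysis already has a survival method.

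**Step 2: crude proportion ever affected.** With a constant rate r per patient-year and follow-up t, the proportion with at least one event is 1 − exp(−r t).

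| Assumed rate per 100 patient-years | 1 year | 8 years | Ratio |
|---|---|---|---|
| 2 | 2.0% | 14.8% | 7.5 |
| 5 | 4.9% | 33.0% | 6.8 |
| 10 | 9.5% | 55.1% | 5.8 |
| 20 | 18.1% | 79.8% | 4.4 |

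Ratios use unrounded proportions. For example, 1 − exp(−0.05 × 8) = 0.3297 and 1 − exp(−0.05 × 1) = 0.0488, ratio 6.8.

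**Step 3: a mixed cohort.** If follow-up were spread evenly over 1 to 8.5 years, the average is 1 − [exp(−r) − exp(−8.5r)]/(7.5r).
- r = 0.05: 1 − (0.9512 − 0.6538)/0.375 = 20.7%.
- r = 0.10: 1 − (0.9048 − 0.4274)/0.75 = 36.3%.

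Neither figure matches the 1-year value (4.9%, 9.5%) or the 8-year value (33.0%, 55.1%) at the same rate.

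**Step 4: can the ranking reverse?** A cohort at 10 per 100 patient-years followed for 2 years gives 1 − exp(−0.2) = 18.1%. A cohort at half that rate followed for 6 years gives 1 − exp(−0.3) = 25.9%. The lower-risk cohort shows the higher crude percentage.

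**Step 5: what removes the dependence.** Under the constant-rate assumption, events per patient-year, or a proportion within a fixed window, have the same expected value whatever the follow-up mix.

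**The case against.** The strongest reply is that the article never says percentages. Events divided by patient-years is itself simple arithmetic, so the wording permits a sound summary as well as a poor one. That stands: the fault is a method named without a time basis, not a demonstrated wrong estimator. A condensed article may also leave denominators and intervals for secondary descriptive outcomes to a fuller plan. That carries weight, but here the article does name a method, in a paragraph that treats time explicitly elsewhere.

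Other limits also stand. Tolerance is undefined and could be a status at a visit or cluster soon after treatment starts, in which case the constant-rate illustration does not describe it. The Conclusions section speaks of treatment and patient outcomes, and it does not say that process outcomes enter the comparison with the literature.

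A reader might infer that all the remaining process outcomes share the problem. The documents do not support that:
- PCC symptom identification comes from a clinic with 1 to 1.5 years of follow-up.
- Screening completion can be a per-visit rate, because section 2.3.3 has adherence documented at every visit, and such a rate need not grow with follow-up.
- NC time to immunotherapy already has survival analysis.

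A reader might also infer that the figures will reflect follow-up as much as quality of care. Nothing in the article allows that to be quantified.

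**Conclusion.** The point holds for EC tolerance and complications only. The analysis plan gives this outcome no time basis, while patients in that clinic are observed for anything from 1 year to about 8 years (7.6 to 8.5 at most, depending on the opening month). A crude ever-affected proportion may then vary about 4- to 7-fold between 1 and 8 years of follow-up, across assumed constant rates of 2 to 20 per 100 patient-years. That size rests on assumed rates and on reading the outcome as an accumulating event. It is a range of what could happen, not an estimate for this clinic. The outcome is secondary, so the primary analyses are untouched, but the result would be hard to interpret against published figures if it is used that way.

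**What to change.** In section 2.3.4, take EC complications and intolerance out of the simple-arithmetic rule. Report them as events per 100 patient-years, as cumulative incidence at fixed times (for example 1, 3 and 5 years, allowing for patients not yet followed that long), or both, with 95% confidence intervals. Every included patient has at least one year of follow-up by design, so the 1-year figure can use the whole EC sample. If tolerance is meant as a status rather than an event, say at which visit it is assessed.

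Add the dates of complications and intolerance to the items extracted from the medical records. The article says that data come from those records but does not say that these dates will be captured. The cost is a little more extraction and analysis work and a short change to the text.

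### The clinic cost total charges each patient exactly one episode, so for the two chronic-disease clinics it does not scale with the care delivered

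*Protocol article*

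**What the plan says.** Section 2.3.4 sets out the costing as a chain. The cost of an activity is staff time multiplied by the unit cost of the staff group. Then: "The cost of an episode of care will be the sum of the costs of all activities on the care pathway". The clinic total follows by "multiplying the cost of each episode of care by the volume of patients treated during the study period". The unit is left to each clinic: "The concept of ‘episode of care’ in this protocol will be determined by the care pathway of the respective clinics".

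Three other statements describe what the total has to cover. Section 2.3.3 introduces the outcomes "For patients with epilepsy or neuroimmunological disorders which are chronic" and says that medication adherence "is documented during each clinic visit", so repeat visits are expected. Section 2.3.4 gives NC and EC outcome data running "from the shortest period of one year to the longest period of eight years". Section 2.3.2 admits patients from each clinic's opening (2013 for NC, 2014 for EC, 2021 for PCC) provided that they "have at least one-year follow-up period as of July 2022 will be included in the study sample".

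Nothing in sections 2.3.2 to 2.3.4 counts episodes, visits or repetitions of an activity per patient, or uses patient-years.

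**The concern.** Time-driven activity-based costing builds a total from how long an activity takes, what the time costs, and how often the activity is done. The plan specifies the first two. For the third it puts in the number of patients. That is adequate where each patient goes through the pathway once. It is not adequate where patients return for years, as in NC and EC.

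Cost is one of the four dimensions of the framework, and section 1.2 presents this costing method as a step towards an accurate estimate of return on investment. A total that is the same whether a patient was seen for one year or eight does not serve that purpose.

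**Working it through.** The article gives no cost, patient number, visit rate or activity time, so there is no figure to reproduce. The check compares the stated formula with the full costing identity.

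**Formulas.** Let c be the cost of one episode and N the number of patients.
- Stated total (2.3.4): c × N.
- Full total: the sum, over patients and activities, of times performed × minutes × unit cost.

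**Within one clinic.** Under the stated formula a one-year patient and an eight-year patient each cost c, a ratio of 1. If care is proportional to time, the ratio should be 8.

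**Case A: an episode is one visit.** Full total ÷ stated total = visits per year × mean years of follow-up. The documents give only the range of follow-up, one to eight years. I assume a mean at its midpoint, (1 + 8) ÷ 2 = 4.5 years, and 1 to 4 visits a year:

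| Visits per year (assumed) | Full ÷ stated, mean 4.5 years | Full ÷ stated, mean 2 years |
|---|---|---|
| 1 | 4.5 | 2 |
| 2 | 9 | 4 |
| 4 | 18 | 8 |

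The factor is 1 only when visits per year × mean years = 1, for example one visit a year over one year.

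**Case B: an episode is a whole course, mapped as T years of care.** If true cost is proportional to years, stated ÷ full = T for a one-year patient, T ÷ 8 for an eight-year patient, and T ÷ 4.5 for the clinic total at the assumed mean:

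| T (years) | One-year patient | Eight-year patient | Clinic total |
|---|---|---|---|
| 1 | 1.00 | 0.125 | 0.22 |
| 4.5 | 4.50 | 0.56 | 1.00 |
| 8 | 8.00 | 1.00 | 1.78 |

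The total is right only if the mapped course happens to match mean follow-up, and it can be wrong in either direction.

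**Activities not given to everyone.** Summing all activities charges each patient for all of them. If half the pathway cost lies in activities that only a share p of patients receive (both assumed), stated ÷ full = 1 ÷ (0.5 + 0.5p). This is 1.60 at p = 0.25, 1.33 at 0.50, 1.14 at 0.75 and 1.00 at 1. It runs against Case A and is smaller. At p = 0.25 the range of 4.5 to 18 becomes 4.5 × 0.625 = 2.8 to 18 × 0.625 = 11.25.

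**The case against.** The strongest reply is that the terms are not yet fixed. Section 2.3.3 says that the pathways are still to be mapped, section 2.3.4 leaves the episode to them, and a patient volume can mean attendances. If it did, and an episode were a visit, the duration problem would vanish. This limits what can be said about size. It does not rescue the formula: the text counts patients treated, and a pathway defined by clinic allows episodes to differ between clinics, not between patients within one. The formula is also explicit in the article, so it is not a detail left to a fuller document.

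Other objections stand and narrow the point:
- The one-to-eight-year range is stated for the outcome models. The costing refers to a study period without dates of its own. A short period would shrink the contrast between patients but could still leave repeat visits uncosted.
- Section 2.3.3 confines the pathway to essential activities, and nothing in the article says that some PCC patients skip some of them. The uptake error is a possibility only.
- PCC is described as acute, so the duration problem belongs mainly to NC and EC.

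A reader might go further and infer three things that the documents do not support:
- **A 32-fold error** (4 visits × 8 years). This gives every patient the maximum follow-up, whereas a clinic total depends on the mean.
- **That the formula hides an effect of team-based care on visit frequency.** The study is single-arm without a usual-care group (section 3), so no costing formula here could show such a change.
- **That surveying current staff is itself an error.** Section 2.3.2 says: "We will survey all HCP involved in delivering care in the three selected clinics at the time of the study". Costing at current practice is a legitimate choice if it is stated.

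**Conclusion.** The point holds in limited form. Followed as written, the NC and EC totals carry one episode per patient and do not reflect the amount of care delivered. This follows from the wording and needs no assumption beyond patients returning, which section 2.3.3 implies.

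The size and direction cannot be derived from the documents. The 4.5- to 18-fold understatement rests on three assumptions: an episode is a visit, patients attend 1 to 4 times a year, and mean follow-up in the costed period is 4.5 years. If an episode is a whole course, the total may be too low, too high or correct by coincidence. An offsetting error from activities that are not universal is possible but smaller under the values tried. The cost of a single episode is not affected by the multiplier.

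**What to change.** In section 2.3.4, state for each clinic what one episode is (a visit, a year or a whole course) and give the dates of the costing period. Replace the patient count with the number of episodes in that period. Alternatively, sum over activities the minutes × unit cost × number of times performed, which also removes any error from activities that not everyone receives. Take the counts from the electronic medical records. Report cost per patient-year for NC and EC, and cost per course for PCC, where care is acute and the endpoint is symptom resolution.

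The cost is a change of wording plus extra data. The records are already to be accessed, but section 2.3.3 lists outcomes, baseline characteristics and treatment regimen for extraction, so visit or activity counts would have to be added. If attendances were meant all along, saying so and defining the episode as a visit would settle the multiplier.
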